## 5. Treatment Plan

(1) Equipment Used for the Trial

Type and Specifications: YKY-B.

Moxa sticks: Specifications: 100mm×270mm, provided by Shanxi Yingkaiyuan Biotechnology Co., Ltd.

Moxibustion equipment: Moxa tubes, moxibustion base, fixing adhesive tape, provided by Shanxi Yingkaiyuan Biotechnology Co., Ltd.

(2) Intervention Methods

**Moxibustion Group:**

Selection of Acupoints: Bilateral Zusanli, Shenque, Guanyuan points.

Acupoint Location: Following the 2006 National Standard of the People's Republic of China "Names and Locations of Acupoints" (GB/T12346-2006): the ST36 is located at 3 cun (about 10 cm) below the patella, outside of the anterior crest of the tibia. CV8 is located at the navel, and CV4 is 3 cun directly below the CV8.

Moxibustion Operation:

- Patient lies supine, exposing the skin at the selected acupoints, hands placed on either side of the body.

- The practitioner affixes the moxibustion device base using adhesive tape on the selected acupoints.
- Ignite the moxa stick on the moxibustion cylinder.
- Position the moxibustion device cylinder so that its top is level with the bottom of the device base.
- Rotate the moxibustion cylinder to adjust the air outlet size, maintaining a distance of approximately 3cm from the skin; make participants feel comfortably warm without burning pain.
- When the warm feeling diminishes, indicating the moxa stick is burnt out, it can be replaced.
- After 60 minutes of moxibustion, close the air outlet, remove the moxibustion device, and place the extinguished moxa stick in a container with water.
- Check the moxibustion device for damage and store it back in the original packaging for future use.
- Each participant undergoes moxibustion once a day (8:00-12:00 AM or 2:00-5:00 PM), 60 minutes per acupoint, five times a week (with weekends off), 12 weeks (60 sessions) in total.

**Sham Moxibustion Group:**

Selection of Acupoints: Same as the Moxibustion Group.

Acupoint Location: Same as the Moxibustion Group.

Shame Moxibustion Operation:

- Patient lies supine, exposing the skin at the selected acupoints, hands placed on either side of the body.
- The practitioner affixes the modified moxibustion device base (equipped with a thermal insulating metal membrane) using adhesive tape on the selected acupoints.
- Ignites the moxa stick on the moxibustion cylinder.
- Positions the moxibustion device cylinder so that its top is level with the bottom of the device base.
- Rotates the moxibustion cylinder to adjust the air outlet size, maintaining a distance of approximately 5cm from the skin.
- Replace the moxa stick after 30 minutes.
- After 60 minutes of moxibustion, close the air outlet, remove the moxibustion device, and place the extinguished moxa stick in a container with water.
- Check the moxibustion device for damage and store it back in the original packaging for future use.
- Each participant undergoes moxibustion once a day (8:00-12:00 AM or 2:00-5:00 PM), 60 minutes per acupoint, five times a week (with weekends off), 12 weeks (60 sessions) in total.

**Blank Control Group:**

The blank control group will receive no treatment and will be instructed not to undergo any interventions that might affect cardiorespiratory fitness until the trial is completed. Measurements for the blank control group will follow the designated time points as the Moxibustion and Sham Moxibustion Groups.

-----

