### **(4) Moxibustion, which tonifies Qi and nourishes blood, contributes to improving cardiorespiratory fitness**

Currently, the primary strategy and method for enhancing and providing cardiorespiratory fitness primarily involve aerobic exercise. This approach is more suitable for athletes and younger individuals. However, for elderly individuals, there exists substantial individual variability in the intensity threshold for aerobic exercise. It becomes challenging to control exercise intensity and volume, thereby inevitably increasing the risk of exercise-related accidents. Hence, there is a necessity to explore

methods that are suitable for improving cardiorespiratory fitness in accordance with the physical characteristics of elderly individuals. Among these, the traditional Chinese medicine technique of moxibustion warrants deeper exploration.

Studies indicate that moxibustion, by warming and promoting circulation, not only facilitates the unblocking of meridians and regulates the circulation of Qi and blood but also warms and nourishes Qi and blood, meeting the needs of the body's organ tissues for Qi and blood. Experimental research demonstrates: moxibustion can prolong exhaustion time in normal rats during exercise; it can alleviate damage to tissues and cells in the liver, heart, skeletal muscles, kidneys, etc., caused by high-intensity exercise, thus alleviating fatigue. Additionally, moxibustion can elevate muscle glycogen and liver glycogen levels in rats during exercise training, ensuring the supply of glucose to tissues such as nerves and muscles during high-intensity exercise, thereby enhancing physical performance. Research on moxibustion's ability to enhance endurance and fatigue resistance demonstrates the clinical value and potential advantages of moxibustion techniques in improving and enhancing cardiorespiratory fitness.

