##### **(2) Exclusion Criteria:**

- Acute stage of serious diseases, such as acute myocardial infarction, acute myocarditis, unstable angina;
- With any other absolute contraindications to CPET or the Six-minute walk test (6MWT);
- With any underlying diseases, such as hypertension, diabetes, coronary heart disease;
- Currently using other Chinese and Western medicines that affect the results of this study;
- Other physical injuries that affect the evaluation of observation indicators, such as lower extremity pain, nerve and muscle diseases;
- Respiratory symptoms within one month;
- Other conditions that may reduce the possibility of enrollment or complicate enrollment, such as frequent changes in the living environment, are likely to cause a loss of follow-up.

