##### **(3) Dropouts:**

- Participants experiencing severe adverse events, as judged by the physician, necessitating termination of their clinical trial participation.
- Occurrence of significant deviations during the implementation of the clinical trial protocol, such as poor compliance, difficulties in evaluating moxibustion efficacy, etc.
- Significant lifestyle changes including but not limited to alterations in diet, and exercise habits.
- Weight fluctuation of more than 5kg.
- Participants express unwillingness to continue the clinical trial during the trial process and request to withdraw from the study under the overseeing physician.
- Unforeseen circumstances hindering the participant's involvement, such as severe accidents, sudden serious illnesses, or death.

(4) Handling of Dropouts:

Dropout Criteria: Participants who, after providing informed consent and being screened as eligible for randomization, fail to complete the specified treatment or observation period according to this protocol will be considered dropout cases.

Handling of Dropouts:

- Researchers should attempt to contact participants who drop out through home visits, scheduled follow-ups, phone calls, letters, etc., to inquire about the reasons for withdrawal, record the last intervention time, and complete as many assessment items as possible.
- In case of dropout due to allergies, adverse reactions, or ineffective treatment, appropriate treatment measures should be taken based on the participant's actual condition.
- All information related to dropout cases should be properly preserved for archival purposes and for statistical analysis in the comprehensive dataset. No additional recruitment of dropout patients is necessary.

(5) Exclusion of Cases:

- Cases that do not meet the inclusion criteria but fulfill exclusion criteria.
- Cases that have not used the experimental intervention.
- Cases without any data after randomization.
- Before statistical data analysis, the decision to exclude cases will be made after discussion among statisticians and principal investigators.

-----

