### **(5) Trial Evaluation Indicators**

- Concomitant Medications: Record the medications taken by participants during the trial, especially those that may influence the study results, such as beta-blockers.
- Dropout and Exclusion Rate Assessment: Detailed statistics on the number, time, assessment status, and reasons for dropout or exclusion during the trial, along with calculation of dropout and exclusion rates.
- Compliance Evaluation: Record the actual number of times participants received moxibustion treatment during the trial. Calculate the ratio of actual treatment received to planned treatment, for compliance assessment.

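### The instruction to avoid other fitness-affecting interventions is written for the blank control arm only, leaving both comparisons with that arm open to co-intervention bias

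*Protocol*

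**What the plan says.** Protocol section 5(2), Blank Control Group, states that this arm receives no treatment and "will be instructed not to undergo any interventions that might affect cardiorespiratory fitness until the trial is completed". Follow-up runs to week 24 (section 6(6)), so the natural reading is that the restriction lasts until then.

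The entries for the other two arms are procedural. The moxibustion entry opens with "Selection of Acupoints: Bilateral Zusanli, Shenque, Guanyuan points" and the sham entry with "Selection of Acupoints: Same as the Moxibustion Group". Each goes on to location, device operation and schedule. Neither mentions other interventions.

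Four provisions are not tied to an arm:
- Section 4(3), Dropouts, lists "Significant lifestyle changes including but not limited to alterations in diet, and exercise habits" and "Weight fluctuation of more than 5kg".
- Section 4(2), Exclusion Criteria, lists "Currently using other Chinese and Western medicines that affect the results of this study".
- Section 6(5) asks staff to "Record the medications taken by participants during the trial, especially those that may influence the study results, such as beta-blockers".
- Section 6(6) collects diet and exercise information at enrolment and at week 12. The entries for weeks 4, 8 and 24 do not list it.

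**The concern.** Background section 1(4) says that "the primary strategy and method for enhancing and providing cardiorespiratory fitness primarily involve aerobic exercise". Participants are enrolled because their fitness is low. VO2peak and anaerobic threshold are primary outcomes and 6-minute walk distance is secondary. All three could move if a participant took up something else that improves fitness.

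If one arm is told in advance not to do so and the others are not, a difference from that arm can reflect what participants were told as well as what the device did. Section 8(1) judges efficacy by statistical differences in the main outcomes, and section 11(2) plans pairwise comparisons among the groups. A difference from the blank arm can therefore support an efficacy claim. Sham versus blank has the same weakness: an apparent sham response could partly be co-intervention. An analysis plan cannot equalise what participants were told.

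**Working it through.** **Step 1. Set the rules side by side.**

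| Rule | Moxibustion | Sham | Blank | When it acts |
|---|---|---|---|---|
| Told to avoid any intervention that might affect fitness (5(2)) | not stated | not stated | yes | in advance, to trial end |
| Significant lifestyle change, or weight change over 5 kg, as dropout ground (4(3)) | yes | yes | yes | after the change occurs |
| Outcome-affecting medicines excluded (4(2)) | yes | yes | yes | at entry |
| Medicines recorded (6(5)) | yes | yes | yes | during trial; records, does not restrict |
| Exercise and diet recorded (6(6)) | yes | yes | yes | baseline and week 12 |

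Only the first row differs by arm. It is also the only rule that addresses participants in advance and the only one that reaches any fitness-affecting intervention.

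**Step 2. Ask whether the common rules close the gap.** They do so in part. A significant change in exercise habits meets the same dropout ground in every arm. Three things remain: change that falls short of significant, for which no threshold is given for exercise; non-drug therapies that are not clearly lifestyle changes; and medicines started after entry, which are recorded only. Dropouts also stay available for analysis (section 4(4)) and missing primary values are carried forward (section 11(1)). A VO2peak value already altered by a co-intervention can therefore remain in the data.

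**Step 3. Identify the comparisons affected.** Moxibustion versus blank and sham versus blank differ in the first row. Moxibustion versus sham does not, since neither arm has the instruction.

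**Step 4. Reproduce the plan's own figures for scale.** Inputs from section 3(2): difference 2.6 ml/kg/min, SD 3.0, 5% significance, 90% power, 15% dropout. Section 11(2) gives two-sided testing.
- Normal approximation: n = 2(1.960 + 1.282)² × 3.0² / 2.6² ≈ 28 per group.
- Two-sample t-test: 28.97, so 29 per group, as stated.
- Dropout: 29 / 0.85 = 34.1, so 35 per group; 3 × 35 = 105, as stated.

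**Step 5. Illustrate what an imbalance would do.** The protocol gives no size for any co-intervention effect, so the imbalances here are assumptions. With no true moxibustion effect and 29 per arm, SE = 3.0 × √(2/29) = 0.788. For an imbalance b, the two-sided 5% false-positive rate is 1 − Φ(1.96 − b/SE) + Φ(−1.96 − b/SE).

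| Assumed b (ml/kg/min) | Share of 2.6 | False-positive rate |
|---|---|---|
| 0.25 | 10% | about 6% |
| 0.5 | 19% | about 10% |
| 1.0 | 38% | about 25% |
| 1.5 | 58% | about 48% |

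**Step 6. What might produce such a b.** Take b as the difference in uptake times the gain in those who take it up. Assume 10% to 30% more uptake and a gain of 1 to 3 ml/kg/min. Then b runs from 0.10 × 1 = 0.1 to 0.30 × 3 = 0.9, or 4% to 35% of 2.6. The upper end is hard to square with section 4(3): a 3 ml/kg/min gain exceeds the whole target difference and would probably need an exercise change large enough to count as significant.

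**The case against.** The strongest reply is that exercise is already controlled in every arm. A reader might infer from section 5(2) that moxibustion and sham participants are free to exercise as they like. The protocol does not support that: a significant change in exercise habits is a dropout ground for everyone, its wording is open-ended, and exercise is recorded in all arms at the end of treatment. This stands, and it narrows the problem to the residue in step 2. It does not remove it, because a dropout ground is not an advance instruction and works by taking people out after randomisation.

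The direction can also be disputed. Untreated participants who know their allocation may have the strongest motive to look for help elsewhere, and the instruction may be there to prevent that. The active arms already attend five times a week for 12 weeks, and nothing in the protocol says they would add exercise. This stands against any claim that the net bias is known. The unequal rule by itself still pushes towards the arms without it, provided that what those arms take up is helpful.

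Finally, the entries for the active arms are device procedures, and consent pages are not part of the copy reviewed. A general instruction may exist in participant material. If so, the protocol should say so, because as written it gives the instruction to one arm only.

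**Conclusion.** The asymmetry is in the text and is avoidable. It leaves moxibustion versus blank and sham versus blank open to bias in VO2peak, anaerobic threshold and 6-minute walk distance, through week 24 if trial completion means the last follow-up. The likelier direction favours the arms without the instruction, on the assumption that they take up more helpful co-interventions than the blank arm.

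Two stronger readings should be resisted. One is that the comparison with blank is shown to be biased in favour of moxibustion by a stated amount. Uptake and effect are both unknown, and every figure in steps 5 and 6 rests on assumptions from outside the protocol. The other is that the whole trial is compromised. Moxibustion versus sham, the comparison that isolates heat and radiation, carries the same rules in both arms and is untouched by this point. The stated sample size reproduces and does not change.

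**What to change.** Move the existing blank-arm instruction into a paragraph common to all three arms, in the same words apart from the assigned study procedure, and for the same period. State the end of that period explicitly. Reconcile the paragraph with section 4(3), so that what participants are told and what counts as a dropout ground fit together.

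Record exercise and other co-interventions, including non-drug therapies, in every arm at the visits already scheduled at weeks 4, 8, 12 and 24, and report them by arm. This lets a reader see whether the arms differed.

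The cost is one protocol paragraph, the matching participant instruction and a few questions at existing visits. No participants or visits are added. If the trial is under way, section 12(1) requires the revision to go back to the ethics committee first.

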## **6. Assessments**

### **(1) General Recording Items**

Participant code, initials of the participant's name in Pinyin, and trial start date.

### **(2) Observation Indicators**

- Biological Indicators: Demographic Characteristics: Gender, age, height, weight.
- Vital Signs: Body temperature, resting heart rate, respiration, blood pressure (systolic and diastolic) after 10 minutes of rest.

### **(3) Diagnostic Indicators**

- CPET Results: Peak Oxygen uptake ( $VO_{2peak}$ ).
- Six-Minute Walk Test Results: Distance covered in six minutes (6MWD).

### **(4) Outcome measures**

- **Primary Outcome Measures: Peak Oxygen Uptake ( $VO_{2peak}$ ) and Anaerobic Threshold (AT)**

The assessment process is as follows:

The CPET procedure involves the following steps: ① Participant completes a health screening questionnaire; ② Participant wears loose, comfortable exercise attire, avoids heavy meals or prolonged fasting before testing, refrains from smoking or consuming strong coffee, and prepares a cup of water; ③ Guidelines and precautions are provided for the evaluation; ④ Participant familiarizes themselves with the exercise protocol, equipment, and pedal speed (50-60r/min), wears a mouthpiece and nose clip to prevent air leakage, adjusts the exercise bike's seat and handlebar height to the most suitable position, becomes acquainted with the Borg Rating of Perceived Exertion scale, common reasons for stopping exercise, and non-verbal communication methods when feeling significantly uncomfortable during exercise; ⑤ The test physician assesses the participant, selects an appropriate exercise power scheme; ⑥ Execution of the scheme under the guidance and supervision of the test physician; ⑦ After the test, the assessing physician extracts and records the participant's  $VO_{2peak}$  and AT value for subsequent data analysis.

Considering the physiological characteristics of older adults and to ensure the completeness and smoothness of the experiment, the trial plans to use the Ramp scheme for the power bike to increment the load. The specific method is as follows: Calculate according to the formula: Predicted unloaded  $VO_2$  value (predicted unloaded  $VO_2 = 150 + [6 \times \text{body weight (kg)}]$ ) and predicted  $VO_{2peak}$  ( $[\text{height (cm)} - \text{age}] \times 20$  (males) or  $\times 14$  (females)). It is generally recommended to complete the incremental exercise test

within 6-10 minutes. If completed in 10 minutes, the increase in power (W) per minute =  $[\text{predicted VO}_{2\text{peak}} - \text{predicted unloaded VO}_2]/100$ . However, the power increment speed is not fixed. For older adults with low daily activity levels or underlying cardiovascular or respiratory system diseases, consider reducing the power increment range.

The specific testing procedure includes: ① Resting phase (3 minutes): Obtain resting heart rate, blood pressure, electrocardiogram, static gas metabolism, and other indicators; ② Unloaded warm-up exercise phase (3 minutes): Maintain a cycling speed of 55-65 r/min, record heart rate, blood pressure, electrocardiogram, blood oxygen saturation, etc., close to the end; ③ Power load phase (6-10 minutes): Maintain cycling speed at 55-65 r/min, closely observe participant's symptoms, heart rate, blood pressure, gas metabolism indicators, blood oxygen saturation, and changes in the electrocardiogram. Note potential adverse reactions during the test, such as angina, breathing difficulties, dizziness, paleness, sweating, significant rapid or slow arrhythmias, ischemic changes in the electrocardiogram, blood pressure drop, shock, etc. If any of these symptoms or signs appear during exercise, the test should be immediately terminated, and appropriate observation and treatment should be given; ④ Recovery phase (6-8 minutes): Maintain slow cycling without load for 2-3 minutes, cycling speed can be maintained at 30-40 r/min, observe the participant's heart rate, blood pressure, electrocardiogram, and symptoms. Stop cycling without load, and continue observing whether the participant's vital signs such as heart rate and blood pressure return to pre-test levels. If symptoms and/or abnormal signs persist for more than 15 minutes after terminating exercise, further observation or treatment is required.

• **Primary Outcome Measures: Serum Central Carbon Metabolites (CCB)**

The main steps of the detection process include sample collection, target metabolite extraction, standard curve establishment, LC-MS/MS detection, and data analysis.

① Instrumentation used: AB Sciex QTRAP® 6500+ Mass Spectrometer, AB Sciex Exion LC™ Liquid Chromatography. ② Reagents: 34 central carbon-related substance standards and 5 stable isotope-labeled standards purchased from Shanghai Zhenzhun Biotechnology Co., Ltd.; Methanol, Acetonitrile, Formic acid, Ammonium acetate (LC-MS, Thermo-Fisher, USA), Aminomethanediphosphonic acid (Sigma-Aldrich, USA), Milli-Q ultrapure water (Millipore, USA). ③ Sample collection: Participants fasted and venous blood was collected in the hospital laboratory. Blood was allowed to clot at room temperature in a centrifuge tube or vacuum blood collection tube for 1 hour. Then centrifuged at 3000rpm for 10 minutes, the supernatant was transferred into 1.5mL centrifuge tubes (0.2mL per tube). After labeling, samples were rapidly frozen in liquid nitrogen for 15 minutes and stored at -80°C. ④ Preparation of standard solutions: Accurately weighed 34 central carbon-related substance standards to prepare a mixed standard solution with a concentration of 100μg/mL. Methanol was used to dilute the

linear mother liquor to obtain working solutions of various concentrations. Solutions of D-Glucose-13C6, (s)-Malicacid-D3, Succinic acid-D4, dAMP lithium salt-15N5, and D-Glucose-6-phosphate disodium salt-13C6 were prepared at certain concentrations and mixed to obtain an internal standard solution (IS). Mother liquor and working solutions for linearity, internal standards, and quality control were stored at -20°C.

Metabolite extraction: Take 100mg of sample and add 500µL of mixed internal standard solution (methanol: water = 4:1). Mix well, stand for 5 minutes, centrifuge at 12000rpm for 10 minutes, and take the supernatant for LC-MS analysis. ⑤ Chromatographic and mass spectrometric methods: Chromatographic column: Waters Atlantis Premier BEH Z-HILIC (2.1×100mm, 1.7µm); Mobile phase: Phase A: 15mM Ammonium acetate + 10µm Aminomethanediphosphonic acid aqueous solution; Phase B: 15mM Ammonium acetate/Acetonitrile; Column temperature: 50°C; Injection volume: 2µL; Flow rate: 0.4 mL/min. Mass spectrometry conditions: Electrospray ionization (ESI), negative ionization mode. Ion source temperature at 550°C, ion source voltage at -4500V, curtain gas at 35psi, and both nebulizer gas and auxiliary gas at 60psi. Multiple reaction monitoring (MRM) was used for scanning.

- **Secondary Outcome Measures: Six-Minute Walk Test (6MWT)**

The test site and standardized execution criteria are as follows: ① Test Site Setup: Select a long, straight, flat, hard-surfaced corridor, 2-3 meters wide, and 30 meters long, with markings every 3 meters. A brightly colored strip is placed on the ground as the start and finish line, with a prominent traffic cone at the turning point. ② Test Physician Preparation: Preparation includes a timer, lap counter, pulse oximeter, blood pressure cuff, test record sheet, portable chair, etc. ③ Participant Preparation: Participants wear loose, comfortable athletic shoes, socks, and clothing. They should avoid heavy meals or prolonged fasting before the test. During the test, participants can use their daily walking aids, such as canes or walkers. ④ Explanation to Participants: The test physician explains the purpose, principles, and procedures of the 6MWT to the participants, including information about taking breaks midway and resuming the test. ⑤ Participant Readiness: Before the test, participants rest on a chair near the starting point for at least 15 minutes. The physician checks for potential contraindications, collects basic information on the test form, measures arterial blood pressure, heart rate, and oxygen saturation, and evaluates the patient's baseline dyspnea and fatigue using the Borg scale. ⑥ Test Initiation: Participants begin the test, and the physician guides, encourages, reminds, and monitors participants at fixed time intervals using standardized verbal cues. ⑦ Complete record of test data, including participant information, actual distance covered in the 6MWT (in meters), percentage of the actual distance to the predicted value, heart rate, blood pressure, oxygen saturation, and any stops or rest taken during the test.

- **Secondary Outcome Measures: the Short Form 36 Health Survey (SF-36)**

The Short Form 36 Questionnaire (SF-36) is used to assess the quality of life in elderly individuals. The SF-36 is a concise health survey that comprehensively covers eight aspects of participants' quality of life, including physical functioning, physiological role limitations, bodily pain, general health perceptions, vitality, social functioning, emotional role limitations, and mental health. Portions related to physical functioning, physiological role limitations, vitality, etc., directly reflect the impact of changes in cardiorespiratory fitness on the quality of life in elderly individuals.

Scoring Method for SF-36:

Converted Score = (Actual Score - Lowest Possible Score for the Aspect) / (Difference between the Highest and Lowest Possible Scores for the Aspect) X 100

Unanswered items are considered missing. The score for missing items is replaced with the average score for the relevant aspect.

- **Secondary Outcome Measures: the Qi and Blood State Questionnaire (QBSQ)**

The Traditional Chinese Medicine Constitution Scale is a standardized questionnaire used to identify traditional Chinese constitutions. Developed collaboratively by the China Academy of Chinese Medical Sciences and Beijing University of Chinese Medicine, this questionnaire evaluates nine types of constitutions, including Qi Deficiency, Blood Stasis, and Qi Stagnation. This study uses Qi Deficiency, Blood Stasis, and Qi Stagnation scales to determine participants' Traditional Chinese Medicine Qi and Blood states.

Specific evaluation process: ① Selection of Assessors: Clinical experienced TCM practitioners with a foundation in TCM theories are chosen as assessors. ② Questionnaire Completion: Assessors question participants based on items in various scales, and participants choose the most suitable answers based on personal experiences and feelings. ③ Score Calculation: Based on the completed questionnaire, assessors calculate the direct and converted scores for participants in different constitutional types. They then determine whether the participant's constitution is "Yes," "Tendency Yes," or "No" based on the scores.

Scoring Method for Traditional Chinese Medicine Constitution Scale:

Raw Score = Sum of Scores for Each Item

Converted Score = ((Raw Score - Number of Items) / (Number of Items × 4)) × 100%

Constitutional judgment based on the converted score: "No" for scores <30, "Tendency Yes" for scores between 30-39, and "Yes" for scores ≥40.

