## **3. Experimental Design Type, Principles, and Procedure**

(1) Experimental Design Type: Randomized Controlled Trial

(2) Principles of Experimental Design:

Sample Size Calculation:

The sample size was determined based on our prior pilot investigation. A mean difference in  $VO_{2peak}$  of  $2.6 \text{ ml} \cdot \text{kg}^{-1} \cdot \text{min}^{-1}$ , with a standard deviation (SD) of 3.0 was observed between the moxibustion and control groups. The estimation conducted via the website (<https://sample-size.net/sample-size-means/>). Approximately 29 participants each group are needed to detect a clinically significant difference in outcome measures at a 5% significance level and 90% statistical power. Considering an estimated dropout rate of 15%, the final sample size required will be 35 for each group, resulting in 105 participants. To recruit this number of participants, we anticipate a study period of 9 months based on our pilot study.

Randomization: Stratified Random Allocation

Control: The study includes apparently healthy elderly individuals, with no underlying diseases. Based on recognized principles of effectiveness, safety, and comparability,

sham moxibustion and no intervention are chosen as controls.

-----

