## 11. Statistical Analysis

### (1) Statistical Analysis Plan and Statistical Software

- Full Analysis Set: Refers to the ideal set of participants as close as possible to the intention-to-treat principle (mainly analyzing all randomized participants). This dataset is derived by excluding participants from all randomized participants in the least and reasonable manner. For missing values of the primary variables, carry-forward estimation will be used, bringing forward the results closest to a single observation of the missing data in the trial, and ensuring consistency between the number of participants evaluated for efficacy at the endpoint and those at the start of the trial.
- Statistical Analysis Contents: Actual number of enrolled participants in three groups, dropout and exclusion cases, demographic and other baseline characteristics, compliance, efficacy analysis, and safety analysis.

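### The SF-36 rule fills every unanswered item with an aspect average and sets no minimum number answered, so an aspect can be scored from a single reply

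*Protocol*

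**What the plan says.** The protocol lists the SF-36 as a secondary outcome (section 6, Outcome measures). It describes the instrument as one that "comprehensively covers eight aspects of participants' quality of life" and names physical functioning, physical role limitation and vitality as the parts that reflect a change in fitness. Each aspect is rescaled to 0–100 by a formula that begins "Converted Score = (Actual Score - Lowest Possible Score for the Aspect" and divides by the possible range.

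The handling of blanks is two sentences: "Unanswered items are considered missing", and then "The score for missing items is replaced with the average score for the relevant aspect". Nothing in that section limits how many items may be filled or says when an aspect score should be left missing.

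The only other missing-data rule is in section 11(1): "For missing values of the primary variables, carry-forward estimation will be used". It covers primary variables, so it does not reach the SF-36. Section 11(2) has no item-level rule. Under section 6, Observational Time Points, the SF-36 is collected at baseline and at weeks 4, 8, 12 and 24.

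**The concern.** An unconditional replacement rule treats a form with one blank and a form with nine blanks in the same way. Both yield an aspect score that enters the analysis with equal weight. A score resting on one or two replies is mostly noise around what the full scale would have shown. If people tend to leave out the harder physical items, it is also tilted towards the easier ones. A wholly blank aspect has no replies to average, so the sentence could then be satisfied only with other participants' values.

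At stake is the quality of the secondary quality-of-life comparisons, at five visits, on the aspects that the protocol itself regards as most relevant to fitness.

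**Working it through.** **The plan's own figures.** The plan gives no figure for this rule. Its only calculation is the sample size for peak oxygen uptake. With a difference of 2.6, SD 3.0, two-sided 5% and 90% power, the exact t calculation gives 29 per group (power 0.9003). Then 29/0.85 = 34.1, rounded up to 35, and 3 × 35 = 105. It reproduces, and nothing below depends on it.

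**Step 1: what the rule does with the participant's own mean.** Filling blanks with the mean of the answered items leaves the average over all items equal to the average over the answered ones. The score is therefore that of a shorter scale. Assume 10 items scored 1–3, with a single reply *a*. The filled total is 10*a*, and the converted score is (10*a* − 10)/(30 − 10) × 100, which is 0, 50 or 100 for *a* = 1, 2 or 3. No other value is possible.

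**Step 2: reliability of the shortened score.** The protocol gives neither scale lengths nor reliabilities, so all of these are assumed. By Spearman-Brown, with *k* items and full-scale reliability *R*:

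- single item: r₁ = R/(k − (k − 1)R)
- *m* items: r_m = m·r₁/(1 + (m − 1)r₁)

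| Assumed scale | Items answered | Reliability |
|---|---|---|
| k = 10, R = 0.90 | 1 | 0.90/(10 − 8.1) = 0.474 |
| | 2 | 0.947/1.474 = 0.643 |
| | 5 | 2.368/2.895 = 0.818 |
| k = 4, R = 0.80 | 1 | 0.80/(4 − 2.4) = 0.50 |
| | 2 | 1.00/1.50 = 0.667 |

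**Step 3: range over the assumption.** For 10 items with common inter-item correlation ρ, the variance of a mean of *m* items (unit item variance) is v_m = ρ + (1 − ρ)/m. The correlation of that mean with the full score is √(v₁₀/v_m).

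- ρ = 0.3: v₁₀ = 0.37. One reply: √(0.37/1.00) = 0.61. Five replies: √(0.37/0.44) = 0.92.
- ρ = 0.7: v₁₀ = 0.73. One reply: √(0.73/1.00) = 0.85. Five replies: √(0.73/0.76) = 0.98.

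Across that range, one reply is a poor to moderate stand-in for the scale, while half the items are a good one.

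**Step 4: how much the source of the average matters.** Keep the 10 items scored 1–3 and one reply *a*, but fill the other nine with a mean *g* taken from other participants, assumed to lie between 1.5 and 2.5. The score is (a + 9g − 10)/20 × 100.

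- a = 1: from (1 + 13.5 − 10)/20 = 22.5 to (1 + 22.5 − 10)/20 = 67.5, against 0 with the own mean.
- a = 3: from (3 + 13.5 − 10)/20 = 32.5 to (3 + 22.5 − 10)/20 = 77.5, against 100 with the own mean.

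**Step 5: effect on the arm comparison, only if the mean is pooled across arms.** Suppose a share *s* of items is filled with one common value in both arms, and items contribute equally to the difference *D*. The expected difference becomes (1 − s)D. With s = 0.30 (assumed), it is 0.70*D*.

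**The case against.** The strongest objection is that this is incomplete wording and not an error. Filling a blank with an aspect average is the same basic device that the fix keeps. Scoring detail often sits in an analysis plan or scoring guide, which is not at hand. That carries weight for the question of whose average is meant. It does not dispose of the missing minimum: the protocol states a rule without conditions, so a later document that added a threshold would depart from it.

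A reader might infer three stronger things that the text does not support.

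- *That the protocol fills scales with other people's values.* The sentence follows a formula built on a respondent's actual score for an aspect, so the participant's own answered items are the natural reading. Only a wholly blank aspect would force the other one.
- *That the arm difference is shrunk and its standard error understated.* This needs a mean pooled across arms. An arm-specific mean would not shrink the difference, nor would the participant's own mean act through this mechanism.
- *That a 0–100 aspect score could be put in an item's place, giving totals above 100.* This is implausible, since the converted score is calculated after the blanks are filled.

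It is also fair to say that sections 10(1) and 10(4) require complete recording, range and logic checks, and queries before lock. These make heavily blank forms less likely, but they set no scoring limit.

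**Conclusion.** The point holds in a narrow form. The protocol replaces every unanswered SF-36 item without a minimum number answered, so one reply is enough to score an aspect. Not saying whose average applies is a lesser gap in wording.

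The size cannot be stated, because no rate of item non-response is given. The reliabilities of about 0.47, 0.64 and 0.82 describe a single participant's score under an assumed 10-item scale at 0.90 with interchangeable items. They are not effects on the treatment comparison. If few participants leave more than half a scale blank, the effect on the trial is negligible. The primary outcomes, the sample size and the type I error for the primary comparisons are untouched.

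**What to change.** In section 6, Outcome measures, replace the second of the two sentences on blanks with:

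> A missing item takes the mean of that participant's own answered items in the same scale at the same visit, after recoding, only if at least half of the scale's items are answered; otherwise the scale score is missing at that visit.

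The cut-off of one half is a judgement and does not come from the documents. On the assumed 10-item scale it caps the loss of reliability at 0.90 − 0.82 = 0.08, against 0.90 − 0.47 = 0.43 with one reply. Checking forms for blanks before the participant leaves would reduce the need for any replacement.

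The cost is one sentence and a few secondary-outcome scale scores that become missing. The change does not remove bias from selective skipping: someone who omits the five hardest of ten items would still be scored from the five easier ones.
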